## Abstract

**Background:**

With 7.7 million South Africans currently infected with human immunodeficiency virus (HIV) and 4.8 million currently receiving antiretroviral treatment (ART), the epidemic represents a considerable burden for the country’s resource-limited health system. In response to the health and human resource shortages, task shifting to community health workers (CHWs) and empowering people living with HIV (PLWH) are integral parts of a sustainable ART strategy. Despite the success of the ART programme, South Africa still faces both prevention and treatment challenges. To tackle these challenges, future endeavours need to focus on the role played by the households of PLWH in mediating between the community and PLWH themselves. Building health-enabling “HIV competent” households with the capacity to actively stimulate lifestyles that foster health, offers a potential strategy to tackle South Africa’s HIV-related challenges. The aim of the “*Sinako*: Households and HIV” study is to investigate to what extent and how an intervention can increase HIV competence in PLWH and their households, and subsequently optimise the impact of CHW support on individual ART outcomes.

**Methods:**

The “*Sinako*” study is a cluster-randomised controlled trial with two arms. In the control arm, CHWs offer a standard package of support to PLWH during home visits, focused on the individual. The intervention arm includes both a focus on the individual and the household to enable the patient to self-manage their treatment within an HIV competent household.

A longitudinal mixed methods design is adopted to analyse the data. For the quantitative data analysis, methods including latent cross-lagged modelling, multilevel modelling and logistic regression will be used. To assess the acceptability and feasibility of the intervention and to construct a comprehensive picture of the mechanisms underlying the impact on the household and the PLWH, qualitative data (in-depth interviews and focus group discussions) will be collected and analysed.

**Discussion:**

Stimulating HIV competence in households could be a feasible and sustainable strategy to optimise the outcomes of CHW interventions and thus be important for HIV treatment interventions in resource-limited settings.

**Trial registration:**

Pan African Clinical Trial Registry, PACTR201906476052236. Registered on 24 June 2019.

## Introduction

### Background

To date, 76.1 million people have become infected with human immunodeficiency virus (HIV) and the virus has claimed an estimated 35.0 million lives globally [1]. The HIV epidemic therefore remains one of the world’s largest public health challenges. In absolute numbers, South Africa bears the brunt of the epidemic, with about 7.7 million people living with HIV (PLWH) [2]. Considerable efforts have been made to address the epidemic; 4.8 million PLWH are currently receiving life-saving antiretroviral treatment (ART) in South Africa [3]. This number is further increasing with the adoption of the Universal Test and Treat (UTT) programme. UTT recommends treatment initiation for all people who are HIV positive, regardless of their CD4 count [2]. The massive ART scale-up has transformed HIV into a manageable, chronic illness, shifting HIV care from terminal care to chronic disease management [4].

Transition to a chronic care model is, however, placing an immense burden on the resource-limited health system. Recent estimates suggest that 42.7% of health professional posts in South Africa are vacant [5]. High attrition, underfunded public sector posts, and inefficient management and recruitment processes contribute to the shortage of health professionals [6]. As a response to these human resource shortages, innovative means of delivering long-term care for PLWH have been developed, such as “task shifting” [7]. Task shifting refers to “a process of delegation whereby tasks are moved, where appropriate, to less specialised health workers” [7]. There is clear evidence of the success of this delegation of HIV services from doctors to non-physician clinicians (type I); from clinicians to nurses (type II); from nurses to lay community health workers (CHWs) (type III); and eventually to self-management by PLWH themselves (type IV) [7].

Despite the success of the ART programme and task shifting, South Africa is still faced with challenges in terms of prevention as well as treatment. With respect to prevention, incidence rates remain high, with about 240,000 new HIV infections in 2018. Furthermore, 700,000 PLWH do not know their status and are therefore not enrolled into care or receiving treatment [1, 3]. Treatment challenges include low rates of adherence and retention in care; only 62% of PLWH are on ART [3], and 23% of patients enrolled in the South African ART programme disengaged from care at least once within a 2-year period [8]. In 2018, an estimated 71,000 PLWH died from acquired immune-deficiency syndrome (AIDS)-related causes [3]. These issues highlight the need to develop innovative and sustainable responses to successfully bring an end to the HIV epidemic in South Africa [1].

To provide effective preventive actions and chronic disease care within the climate of human resource shortages, it is not enough to simply shift responsibility for chronic HIV care to the community (type III) and PLWH (type IV) themselves. Future endeavours need to focus on the search for innovative ways to provide social support in response to these scarcities. A potential source of such support already exists at the intermediate level, between the community (type III) and PLWH (type IV), namely PLWH households. In this study, households are defined as a “co-residential unit, usually family-based in some way, which takes care of resource management and the primary needs of its members” [9].

The intermediate household level is often overlooked in the current chronic disease care delivery model. However, PLWH seldom live in isolation, and their home life is generally regarded as the closest and most basic context for individual development [10]. Previous research has shown that spatial proximity and day-to-day interactions are two characteristics that are vital to the daily provision of care and support to HIV-affected individuals [9]. The direct and indirect impact of transmission risk, care burden, social stigma, physical illness and emotional distress is shouldered by various household members [11]. Living with a chronic illness, such as HIV, is “complex and requires integration of self-management behaviours into the lifestyles of individuals and households” [12]. “Building health-enabling households” that support patients along the care continuum and stimulate positive living offers a potential strategy to tackle the current HIV treatment and prevention challenges [13].

### Theoretical framework

#### HIV competence and health-enabling contexts

In order to address prevention and treatment challenges within the household context extensive efforts are required to increase HIV knowledge, reduce stigma, stimulate HIV testing, improve health care-seeking behaviour, and encourage safe sexual practices—described by UNAIDS and other authors as the need for HIV competence [14, 15]. Achieving HIV competence cannot be done by individuals alone—it is a group phenomenon, since health decisions are seldom made in isolation [14]. HIV competence reflects the idea that “the likelihood that people will choose health-enhancing practices depends not only on individual-level factors, but also on the extent to which they live in social environments that enable and support this choice” [13].

These ideas are rooted in the ecological approach of Kelly et al. [16] with its emphasis on the importance of developing contexts that provide support in strengthening the individual and building social resources to respond to challenges [17]. Such a health-enabling context is assumed to be a responsive environment that stimulates individuals to become health competent by facilitating health-enhancing behaviours and promoting the spread of health information and health norms [16, 18]. In addition, a health-enabling context can support “collective efficacy”, meaning that people can take more control over their lives and their living environment in order to achieve better health [18]. This collective dimension is especially relevant for HIV as “HIV infects individuals and simultaneously affects a whole network of significant relationships” [19].

#### HIV competent households

Integrating the elements of this theoretical framework, the research team developed the theoretical concept of “HIV competent households” based on qualitative research [20] to lay the foundations for this project. In this conceptualisation of HIV competent households, it is shown that the household has the potential to form a health-enabling environment for PLWH. An HIV competent household is an environment in which the patient can be supported across the HIV care continuum in a sustainable manner. HIV competent households 1) gain, share and translate HIV-related knowledge into good prevention and treatment behaviour; 2) create a safe space for disclosure and dialogue about HIV; 3) foster ownership of HIV and responsibility for safe sexual practices, testing and ART; 4) build solidarity to support PLWH in its midst to adhere to ART and remain in care; and 5) are receptive to outside support (e.g. from a CHW) [20].

However, the road to HIV competence in the household is precarious and prone to obstacles at both the individual and household level. As a result of HIV-related stigma both outside and inside the household, the development of HIV competence can easily be undermined. Furthermore, a household’s lack of social support or emotional connectedness, discrimination against HIV or misconceptions about the illness can further inhibit the development of HIV competence at the household level and may even produce a health-impeding context [20]. In such a negative household environment, PLWH might not disclose their status, fearing stigmatisation. Non-disclosure may not only impact ART adherence, but also impacts practices for prevention of transmission to other household members [20]. This potentially health-impeding role of the household underlines the need for comprehensive and context-specific interventions to stimulate HIV competence at the household level [21].

#### The positive communication process as a mechanism of change

Based on the circumplex model of marital and family systems by Olson and the results of qualitative research by Masquillier et al., the research team developed the positive communication process (P^2^CP), which delineates four steps in the process of building HIV competence at the household level [22–24].

The road to HIV competency commences with the recognition of the reality of HIV by the PLWH themselves (P^2^CP step 1). A necessary condition for the building of HIV competence in the household is then disclosure, as household members can only offer social support related to living with HIV when the patient has shared their status (P^2^CP step 2) [25]. Equipped with the correct knowledge and communication skills provided by outside support (e.g. from a CHW), the patient and the confidant are encouraged to become change agents in the household (P^2^CP step 3). They create awareness and openness about the illness in their midst and the need for behaviour change to prevent further transmission to others. These change agents are therefore the motor that will prompt the move towards HIV competence at the household level. Moreover, the change agents will act as “household health advisors” by translating their knowledge and communication skills into positive HIV-related communication dynamics at the household level, such as safe sex negotiation or a conversation about adherence support. An increase in HIV-related knowledge supports the gradual process of normalisation of HIV in the household, which is required to build an environment that is responsive to HIV treatment and prevention. Finally, these constructive household dynamics are translated into HIV competence (P^2^CP step 4), resulting in a household that forms a health-enabling environment in which it is easier for the patient to self-manage their treatment, adhere to ART, and reduce the likelihood of a new HIV infection within the household (for instance, by increased condom use).

### Research aims

In this project, the HIV competent household concept will be advanced beyond the merely theoretical and conceptual level. Building on the existing literature and our preparatory work, the current project aims to investigate empirically to what extent and in what way HIV competent households can become sustainable health-enabling contexts that can provide an answer to the HIV prevention and treatment challenges facing South Africa. To this end, this project—the *Sinako* (‘we can’ in isiXhosa) HIV and households study—aims to test an evidence-based household intervention delivered by CHWs to: 1) increase HIV competence in PLWH and their households; and subsequently 2) optimise the impact of CHW support on individual antiretroviral treatment outcomes.

## Methods/design

### Trial design

The primary activity for the Sinako study will be the implementation and assessment of the impact of an HIV competent household intervention. Table 1 represents a schedule of intervention implementation, assessment and dissemination. The intervention will be assessed in a cluster-randomised control trial (RCT) with two arms. CHWs will be the primary actors in this RCT, either continuing to deliver a standard ART adherence support service (arm 1), or a standard ART adherence support service plus a household P^2^CP intervention (arm 2). CHWs, however, are linked to a health care facility, which creates a risk of contamination when CHWs active in different arms operate from the same facility. The facility was therefore selected as the cluster unit of randomisation. The health care facilities in the study setting were categorised as large or small facilities according to the numbers of CHWs employed, which also corresponds to the number of patients. Subsequently, 12 facilities were grouped by selected subdistricts and were randomly selected from the list of facilities for inclusion in the study in arms 1 and – resulting in six facilities or clusters per trial arm. Further blinding of the study arms was not possible because of the clear differences between the intervention and the standard of care. The design and report of this clinical trial protocol follows the Standard Protocol Items: Recommendations for Interventional Trials (SPIRIT) statement (Additional file 1).

**Table 1 Tab1:** Schedule of intervention implementation, assessment and dissemination

	Year 1	Year 2	Year 3	Year 4
Preparatory research activities				
Ethical approval	X			
Preparatory literature review	X			
Quantitative survey development	X			
Mobile data collection tool programming	X			
Qualitative questionnaire development		X		
Development of the household intervention	X	X		
Pilot of the household intervention		X		
Drawing study sample for cluster-RCT		X		
Fieldworker training		X		
Baseline assessment of HIV competence and HIV outcomes				
Baseline quantitative data gathering, capturing and cleaning		X		
Qualitative data collection		X	X	
Baseline quantitative data analysis			X	X
Writing of reports and articles		X	X	X
Implementing the household intervention				
Workshops providing training to CHWs conducting the intervention		X		
Screen participants for eligibility		X		
Informed consent		X		
Implementing the intervention in the experimental households		X	X	
Monitoring of the intervention using qualitative methods		X	X	
Measuring the impact of the household intervention				
Developing a quantitative postintervention survey		X		
Follow-up quantitative data gathering, capturing and cleaning		X	X	
Focus group discussions on experience of intervention implementation			X	
Follow-up quantitative data analysis			X	X
Qualitative data analysis			X	X
Writing of report and articles			X	X
Dissemination of knowledge on the household competence intervention				
Presenting results at international conferences		X	X	X
Writing of report and articles		X	X	X
Finalising PhDs				X

*CHW* community health worker, *HIV* human immunodeficiency virus, *PhD* Doctor of Philosophy, *RCT* randomised controlled trial

### Study setting and site selection

The cluster-RCT will be executed in the Western Cape Province of South Africa in five health subdistricts of the Cape Metro area: Khayelitsha, Klipfontein, Mitchell’s Plain, Eastern and Western.

Mitchell’s Plain has the largest population of the five subdistricts and is predominantly inhabitated by of Coloureds (91%). In contrast, the population in Khayelitsha is mainly Black African (99%). For the three other subdistricts, race distribution is almost equal between Coloureds and Black African populations, with the Western subdistrict showing a significant presence of the White population (29%). All these subdistricts are confronted with severe social and economic challenges, and poverty is widespread. Unemployment is omnipresent with an average unemployment rate of 28.6%, ranging from 18% in Western to 38% in Khayelitsha. Of the five subdistricts, Khayelitsha is the most impoverished, with more than half of the households living in informal dwellings (55%) and with 74% of households surviving on a monthly income of R3200 or less (approximately US$218). Conversely, the Western subdistrict appears to be a little less disadvantaged than the other five subdistricts, with 15% of households living in informal dwellings and a slightly lower unemployment rate of 18% [26].

These social and economic challenges translate into health-related challenges as a result of limited access to health care, education, intra-partner violence, and transactional sex, among others [27]. According to the national antenatal sentinel HIV and syphilis survey, HIV prevalence in the Cape Town metropolitan area, within which the five subdistricts are located, was 21.6% [28]. Moreover, across the entire Western Cape Province, Khayelitsha was identified as having the highest HIV prevalence, with a seroprevalence of 34.3% among pregnant women [29]. With regard to retention in care after 12 months for ART, Eastern performs best of all five subdistricts included in the study at 71.7%, while Klipfontein has demonstrated the least favourable percentage of retention of patients in care, with 61.6% of the patients retained after 12 months. At 48 months of retention in ART care, a similar pattern can be found: Eastern (58.9%); Mitchell’s Plain (58.5%); Klipfontein (56.3%); Western (56.3%); and Khayelitsha (55.0%) [30].

#### Participants

Inclusion criteria for participants include the following: a minimum age of 18 years; having commenced ART within 4 weeks of enrolment either for the first time or again in the case of previous defaulting; having a household member above 18 years old; not being co-infected with tuberculosis at the time of the test; not tested as a result of pregnancy; accessing HIV care and treatment at one of the designated health care facilities for this cluster-RCT; and living in the area of this facility.

The CHWs participating in this trial were selected through an application process based on various criteria, including: having experience as a CHW supporting people living with HIV; willingness to learn new skills and embrace different methods for supporting ART adherence; and willingness to work in the community, including locating clients and conducting the intervention in the client’s household. Intensive training workshops have been held to train the CHWs recruited in the intervention arm of the RCT about their specific tasks and equip them with the skills to deliver the intervention.

#### Sampling

A sample size of 180 individuals per arm was obtained by sampling 12 clusters in total (six for each arm) with 90% power to determine an increase in ART adherence (primary outcome (see below)) from 68% to 83% (effect size = 15%) postintervention over a period of 12 months. The proportion in arm 1 (the control group) is assumed to be 0.68 under the null hypothesis and 0.83 under the alternative hypothesis. This sample size has been calculated for a two-sided Z test (unpooled) and 5% significance level. The intracluster correlation is 0.0020. The estimated effect size is conservative since this is a new intervention that has not been rigorously assessed in South Africa. We hope to increase the ART adherence levels by 30%; however, we have powered the study on a lower effect size (15%) to avoid a type 2 error. The total sample size of 640 individuals (320 per arm) instead of 360 (180 per arm) will be used to allow for loss to follow-up. As a result of this oversampling to account for loss to follow-up during the trial, CHW will deliver the intervention to a total of 320 PLWH receiving ART adherence support.

#### Recruitment

As part of the standard procedure in the South African health system, the counsellor tests the individual at the clinic. Upon a positive HIV test, the counsellor opens a patient file and scans the patient’s preliminary eligibility criteria. A second clinic visit is then scheduled where the patient will be introduced to their CHW and the study. If the patient refuses to participate, the patient stays in the regular South African health system. If the potential participant agrees, the CHW enrols the individual and schedules a first visit at home or an alternative location preferable to them. At this home visit, the CHW provides further information about the study, invites the PLWH to complete an informed consent form, reassures confidentiality and explains the importance of an interview with a household member. The CHW takes household member names and then schedules the second home visit where the individual baseline interview will be conducted by the fieldworker. The household includes all those people who “eat from the same pot” for at least four nights per week over the past month. Based on the household information document, household members will be randomised by the fieldwork team for the household member interview. If the household member interview is not completed within 30 days of patient enrolment, the household member is not included in the study.

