##### Baseline data collection

For the baseline data collection, the CHW presents the study during the first pre-intervention visit and asks for informed written consent for obtaining contact information of the household members used for the household interview (see section on “Intervention” above). A trained fieldworker joins the CHW during the second preintervention visit. After obtaining informed consent from a PLWH willing to participate in the full study, the fieldworker administers the questionnaire on a hand-held device, using Mobenzi software [34].

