## Ethics, consent and permissions

Before study enrolment informed written consent of all participants is obtained. The consent forms are available in both English, isiXhosa and Afrikaans. The purpose of the study and its design and aspects such as informed consent and confidentiality is explained in an understandable manner to the respondent in the language of their preference (English, isiXhosa or Afrikaans). This information is also distributed by means of an information leaflet which the participants receive from the fieldworker. Written informed consent is required not only for study enrolment, but also for audio recording and for the publication of the findings. After written informed consent, respondents who agree to be included in the study are subjected to either a baseline and follow-up survey or a baseline and follow-up interview plus a household intervention.

Respondents can withdraw from the study at any time without penalty or loss of benefits to which they are entitled. If the respondent faces issues they do not want to discuss, the researcher will be sensitive to the interests of the participants by not pressing the issue and moving on to the next question.

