## Protocol version

An application for funding was submitted in April 2017 to the Research Foundation Flanders and in May 2017 to the VLIR-UOS Research Foundation—Flanders for different aspects of this cluster-RCT. It went through thorough external peer review for each funding organisation separately. Funding was granted for 4 years, starting from January 2018. In November 2018, we applied for additional funding for the qualitative research component via a Global Minds scholarship at the University of Antwerp and in August 2018 for NRF funding. Each funding body reviewed various aspects of the qualitative research component separately. This article is based on the final protocol (version 1, June 2019). Recruitment for the baseline survey and intervention began in year 2 (8 October 2019). We anticipate that recruitment will be completed by year 3 (May 2020). The postintervention survey and the longitudinal qualitative work are expected to be finalised by year 3 (October 2020).

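### Patients are recruited after facilities are allocated, by unblinded CHWs who deliver that facility's arm, so recruitment can differ between arms; the enrolment point is also stated inconsistently

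*Protocol article*

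**What the plan says.** **Order of allocation and recruitment.** Under Trial design: "The facility was therefore selected as the cluster unit of randomisation". Twelve facilities "were randomly selected from the list of facilities for inclusion in the study in arms 1 and" (the second arm number is missing in the text), "resulting in six facilities or clusters per trial arm". The same section says that blinding of the arms was not possible. Under Participants, the training is reported as complete: "Intensive training workshops have been held to train the CHWs recruited in the intervention arm of the RCT". Under Protocol version: "Recruitment for the baseline survey and intervention began in year 2 (8 October 2019".

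**Who recruits.** Under Recruitment, the counsellor does the HIV test and a preliminary eligibility scan. At a second clinic visit the patient is introduced to the CHW and to the study. Then "If the potential participant agrees, the CHW enrols the individual and schedules a first visit at home". At that home visit the CHW gives further information and invites written consent. Under Trial design and Intervention visits, CHWs deliver the allocated support.

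**When consent is taken.** Under Ethics, consent and permissions: "Before study enrolment informed written consent of all participants is obtained". Under Baseline data collection, the CHW's first-visit consent covers contact details of household members. The fieldworker starts the questionnaire at the second preparatory visit, "After obtaining informed consent from a PLWH willing to participate in the full study".

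**Voucher.** Under Quantitative data collection, participants who complete baseline and follow-up receive R75 in control and R150 in intervention.

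**The concern.** In a cluster trial, randomising facilities balances the facilities in expectation. It balances the patients only if they are identified before allocation, or are recruited afterwards by a process that does not depend on the arm. Here neither is described. The person who presents the study, enrols the patient and first asks for consent belongs to one arm, is not blinded and will deliver that arm. What is on offer differs too: control is a pill count, while the intervention adds self-management and household sessions in which disclosure is a recurring theme. Both the way the offer is made and the patient's reason to accept can therefore vary by arm.

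Any resulting difference in motivation, willingness to disclose, or the mix of first-time and restarting ART patients would be read as part of the adherence effect. An intent-to-treat analysis does not remove it, because it arises before the analysis set is formed.

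The unclear enrolment point adds a second problem. The four-week limit since starting ART and the 30-day limit for the household interview both run from enrolment, and the text supports more than one date for it.

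**Working it through.** **1. The plan's own figure.** Inputs from Sampling: adherence 0.68 and 0.83, two-sided 5% unpooled Z test, 90% power, intracluster correlation 0.0020, six clusters per arm.

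- Without clustering: n0 = [0.68×0.32 + 0.83×0.17] × (1.960 + 1.282)² / 0.15² = 167.5 per arm.
- With clustering: solving 6m = n0 × [1 + (m − 1) × 0.002] gives m = 29.51. Rounded up, this is 30 per cluster, or 6 × 30 = 180 per arm, as stated. Power is then 90.4%.

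The sample size is not at issue. It does treat the whole expected difference as treatment effect.

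**2. Size under an assumed selection model.** The protocol gives no data on who accepts, so every parameter here is an assumption. Let U be a standard normal motivation score. Set P(adherent) = expit(0.85 + 0.8U), which averages 67.9%, close to the plan's 68%. Set P(enrolled) = expit(1.4 + kU), where k is the strength of selection on motivation. There is no treatment effect.

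| Slope k, intervention arm | Enrolled | Adherence among enrolled | Difference, control slope 0 | Difference, control slope k/2 |
|---|---|---|---|---|
| 0.3 | 80% | 68.8% | +0.9 points | +0.5 points |
| 0.6 | 79% | 69.8% | +1.9 points | +1.0 points |
| 1.0 | 76% | 71.2% | +3.3 points | +1.7 points |

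The largest value, 3.3 points, is 3.3/15 = 22% of the target difference. Equal slopes in both arms give zero, and stronger selection in control reverses the sign.

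**3. Effect on the test.** Suppose there is no treatment effect and recruitment alone moves intervention adherence from 0.68 to 0.68 + b. The standard error is √{[0.68×0.32 + (0.68+b)(0.32−b)] × [1 + (m−1)×0.002] / n}. The probability of a two-sided p < 0.05 is:

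| b | 180 per arm (m = 30) | 320 per arm (m = 53.3) |
|---|---|---|
| 0 | 5.0% | 5.0% |
| 2 points | 6.8% | 8.2% |
| 3 points | 9.2% | 12.3% |

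A larger sample does not help: the bias stays the same and the standard error shrinks.

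**4. The enrolment point, side by side.**

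- Recruitment: the CHW enrols on agreement at the clinic; written consent is invited later, at the first home visit.
- Ethics, consent and permissions: written consent precedes enrolment.
- Baseline data collection: consent to the full study is taken at the second preparatory visit.

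The first two cannot both hold. The third can be read as a staged consent, but it leaves open which signature starts participation.

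**The case against.** Several things count against a strong reading. Eligibility criteria are the same in both arms, including having an adult household member. Both arms receive similar preparatory visits, with a home assessment and a request for household contact details, and every recruit is told about the household interview. Control CHWs will therefore also meet reluctance about home visits. On the intervention side, visits may take place elsewhere, and bringing a household member is not required to continue. The counsellor screens first, and no section gives CHWs discretion over whom to approach. Under Implementation, recruits in general are patients who return for care and are seen as likely to commit, so some selection on motivation is expected in both arms. Quantitative data analysis mentions control for social characteristics and for medical and medication history.

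Most of this stands, and it limits the claim. A reader might infer that intervention CHWs favour patients open to disclosure while control CHWs apply no filter. The documents do not say so; that is conjecture, and it is why the one-sided column above is an upper case within the assumed slopes. A reader might also infer that patients lost between the consent steps will be left out of the intent-to-treat set. The protocol promises an intent-to-treat analysis, and the exact set may be fixed in an analysis plan that is not shown.

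It does not remove the mechanism. Shared criteria do not make the offer or its acceptance the same. The counsellor's scan is only preliminary and is not said to be made without knowledge of the arm. The covariate sentence follows the latent models and can deal only with measured differences. That control CHWs know their arm is inferred from the lack of blinding and the intervention-only training, but it is a safe inference.

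**Conclusion.** The concern holds as a design weakness. Following the Recruitment section as written allows the arms to recruit different patients, and facility randomisation gives no protection against that. The unequal voucher is a further route by which acceptance could differ, although the protocol does not say when patients learn its value.

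The documents show that bias can arise, not that it has arisen or which way it would go. On the assumptions stated, it is about +1 to +3 points if selection occurs only in the intervention arm, and about +0.5 to +1.7 points if control selection has half the slope. That is modest against 15 points. It could still be mistaken for effect: a 3-point shift alone would raise the false-positive rate from 5% to about 12% with 320 analysed per arm.

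Separately, the statements on when a patient is enrolled conflict and need to be reconciled, whatever the size of any recruitment bias.

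**What to change.** 1. For remaining recruits, have the clinic counsellor, who already screens eligibility, offer the study to consecutive eligible patients with one script that does not reveal the arm.
2. Have the fieldworker take study consent and complete the baseline interview before the facility's package is described to the patient.
3. Use one enrolment point, the first signed study consent, and define the intent-to-treat set from it. Bring Recruitment, Baseline data collection, and Ethics, consent and permissions into line with it.
4. Adjust the primary intent-to-treat comparison for baseline adherence, which is already collected, and for new versus restarting ART.

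Cost: a little counsellor and fieldworker time, a revised script and two covariates. Patients are now introduced to their CHW at the clinic as routine, so the order of steps has to change. If recruitment is under way, the procedure changes part-way; record the date of change by facility so that the two periods can be compared. Adjustment removes only measured imbalance, so item 4 does not replace items 1 and 2.
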